### Participants

The study population consisted of students who attended the following basic courses (vocational clusters in brackets):Car mechanicsCarpenter, bricklayer, painter or plumber (Construction)Electrician, data technician or frontline PC supporter (Electricity and information and computing technology (IT))Media graphic designer, graphic technician, web integrator or sign writer (Media production)Zookeeper, landscaper, farmer or greenhouse gardener (Agricultural)

Shaping the Social is designed to accommodate the fact that this was a heterogeneous population considerably more diverse than, for example, a typical Danish high school population.

### Data collection

The students answered a questionnaire within the first week of their basic course (T0) and at 10-week follow-up (T1). Teachers of the classes that were involved in the intervention answered a questionnaire about implementation at 10-week follow-up. School dropout rates will be tracked via national education registers [28] through a 2-year follow-up period (T2). Table 1 presents an overview of the collected data and the study time path. All residents in Denmark have an unique and permanent personal identification number, which allows individual-level linkage between nationwide registries [29]. In the baseline and 10-week follow-up questionnaire, the students were asked for their personal identification number in order to match the responses between the data collections and to follow up on individuals in registers.

**Table 1 Tab1:** Collection of data and time path

	Instrument	Baseline	Follow-up	
		T0	T1	T2
			10 weeks	2 years
Personal characteristics				
Sex, age, ethnic origin, ethnic identity, parental education [44], family social class, distance to school, living arrangement, having children, quantitative and qualitative aspects of social relations [36], health and health behaviour [36], level of Danish reading and writing, level of prior schooling, prior academic achievement and academic self-efficacy [45]	Self-reported	X		
Primary outcomes				
Student well-being [33]	Self-reported		X	
Cigarette smoking [36]	Self-reported	X	X	
School dropout	Register data			X
Secondary outcomes				
Life satisfaction [39], physical and psychological symptoms [37], loneliness [38], alcohol consumption, use of cannabis and other illicit drugs [36]	Self-reported	X	X	
Immediate outcomes				
Indicators of well-conducted introduction period	Self-reported	X	X	
Indicators of classroom management [33]				
Degree of implementation				
Preliminary meeting at the school with a specialist teacher, the students and their relatives	Teacher reported		X	
Welcoming activities at first school day	Teacher reported		X	
Timetable with a clear description of course, time and clothing requirements	Teacher reported		X	
Class meeting every morning including beverages or food	Teacher reported		X	
Scheduled breaks	Teacher reported		X	
Created a place for hanging out during breaks	Teacher reported		X	
Monthly events during school hours organised across sections, and followed by an open café	Teacher reported		X	
Access to school facilities outside school hours and a member of staff is present	Teacher reported		X	

We developed the student questionnaires with items based on Danish population surveys, and on validated scales when possible. The questionnaires were subject to an expert hearing followed by pilot testing among students (*n* = 117) in three vocational schools (not included in the intervention study). Self-developed items, especially, were giving attention. We kept the questionnaires as short as possible in order to increase the response rate [30].

Data collections were performed during class and took approximately 20 min. Baseline assessment was not possible before school start, because school records of students were incomplete. Moreover, we chose to collect data during school time because the student population included socio-demographically diverse subgroups and a predominately male and young population, which are characteristics that can predict non-response [31, 32]. Questionnaires were web-based with an audio voice-over so the students heard questions through headphones while they appeared on screen. Follow-up of non-respondents in the 10-week-follow-up assessment was by electronic mail, mobile text message and a mailed letter.

Baseline data collection started in October 2011 and ended in October 2012, and comprised five samples of basic courses (autumn 2011, winter 2012, spring 2012, summer 2012 and autumn 2012).

### Outcome measures

Our primary outcomes were student well-being at school, smoking and school dropout.

*Student well-being* was conceptualised as positive student interpersonal relations, positive student-teacher relations, school connectedness and positive valuing of the profession, and was measured on items developed for the Danish version of the Health Behaviour in School-aged Children (HBSC) surveys [33] and new items. The HBSC measures is designed to capture a broad conception of student well-being at school and have been piloted for international use in samples of 13- and 15-year-old students and have shown adequate validity and reliability [34]. Student interpersonal relations were measured by a 5-item HBSC classmate support scale (e.g., ‘the students in my class enjoy spending time together’). Student-teacher relations were measured on a 3-item HBSC scale (e.g., ‘I feel that my teachers accept me as I am’). School connectedness was measured by three HBSC items (e.g., ‘I feel I belong at my school’) [35]. Valuing of the profession was measured by four Shaping the Social items (e.g., ‘I am proud of my profession’).

*Cigarette smoking* was measured by daily smoking status (yes, no) and current number of cigarettes smoked per day [36].

*School dropout* will be tracked by national education registers from Statistics Denmark. The students will be categorised into one of the following categories: (a) completed the basic course, (b) still registered in the basic course or changed to another upper secondary education, (c) dropped out from basic course and has not attained another upper secondary education.

For secondary outcomes we assessed well-being in general by physical and psychological symptoms measured on the HBSC Symptom Checklist (e.g., difficulty sleeping) [37], loneliness measured by one item [38], and life satisfaction measured on the Cantril Ladder Scale [39] with ten positions ranging from zero (the worst possible life) to ten (the best possible life). For unintended effects we assessed alcohol consumption and use of cannabis and other illicit drugs than cannabis (e.g., cocaine) [36]. We measured alcohol and drug consumption as side-effects but it is difficult to predict whether they will occur as unintended adverse or positive effects. Increased school well-being has a positive impact on alcohol and drug use [40]. However, the literature also indicate that young people who have an active social life have more drunkenness-oriented drinking patterns and are experimenting more with drugs [41].

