## Background

Schools are important settings for health promotion in young people [1–5]. Health education aiming to improve knowledge, develop skills and modifying norms is frequently used in schools, for example addressing substance use. However, such interventions often have disappointing results [6, 7]. In recent years there has been an increased recognition of how modifying the school social and/or physical environment can promote students’ health [8–10]. For example, a review found that class restructuring programs in which students spend more time with teachers were effective in decreasing school dropout [10]. Such a comprehensive approach is also known as the healthy school setting approach [11]. However, the evidence for this approach is relatively weak, in part because of difficulties related to both implementation and evaluation [12].

Several longitudinal studies have shown that harmful substance use predicts poor educational achievement [13, 14] and that educational failure is predictive of harmful substance use [15, 16]. Thus, a comprehensive perspective on both health risk behaviour and school dropout should be considered in intervention programmes aiming at promoting health and educational attainment.

In Denmark, approximately half of students drop out of vocational schools, which is a much higher rate compared to 18 % high school dropout [17]. The educational programme at vocational schools consist of a short basic course (typically 10–40 weeks) followed by a main course. Most dropout occurs during basic training. In addition, students more often engage in health risk behaviour compared to high school students [18]. For example, 23 % of vocational students and 9 % of high school students have tried drugs other than cannabis [18].

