### Setting

After nine compulsory years of primary and lower secondary school, almost all young people of Denmark choose to continue into the academically oriented upper secondary schools system, which is preparing students for tertiary education or into vocational education organized in separate schools spread out across large and medium sized cities. About 23% will choose vocational education [27]. Vocational education includes commercial, agricultural, technical, and social and healthcare programs leading to professions such as farmer, carpenter or web integrator. All programs are initiated by a school-based basic course lasting 20–25 weeks. The basic courses usually started four times a year and are flexible in duration depending on the student’s prior qualifications and ambitions. This means that some students within a class finish the basic course before others, and therefore a class is not a definite unit. Additionally, the high dropout rate implies that classes are merged during the basic course. We defined a class as students entering the same programme (e.g., carpenter) on the same date at the same address.

The vocational schools are organized into two levels. The upper level is the school with a management board. Next level is departments (e.g., construction) which are each headed by an inspector, one or more educational managers and an administration manager, and, typically, the departments have separate physical area and culture. In Shaping the Social, the upper analyze level will be these departments within schools (named college units).

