### Study strengths and limitations

The strength of Shaping the Social is the relatively high response rate at the baseline survey, which may have been due to our efforts to collect data during school hours. Dropping out of school is a condition of the vocational school setting, which adversely affected the retention rates. However, the high submission of the personal identification number in the baseline survey makes it possible for us to link data to education registers at an individual level. Thus, we will be able to determine the intervention’s long-term effect on educational attainment.

The aspect that creates the intervention’s potential success (its settings-based comprehensiveness) also creates potential difficulties in analysing its effectiveness. The variety of factors that contribute e.g., to student well-being makes it challenging to clearly distinguish between successful and unsuccessful characteristics of the programme. The intervention’s comprehensiveness (establishment of new school practices and re-shaping existing practices) rules out a highly standardized intervention. This is addressed by collecting and analysing teacher data with respect to the school practices [42]. However, it proved infeasible to collect teacher data with respect to intervention components at the comparison schools. This may led to underestimation of effects, if the existing practices at comparison schools are similar to the intervention.

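### The register dropout outcome is defined only on the basic course, so it does not by itself support the stated long-term effect on educational attainment

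*Protocol article*

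**What the plan says.** School dropout is one of three primary outcomes. Outcome measures says of the register data: "The students will be categorised into one of the following categories". The first two categories are "a) completed the basic course, (b) still registered in the basic course or changed to another upper secondary education", and the third is "c) dropped out from basic course and has not attained another upper secondary education". Data collection and Table 1 place this outcome at T2, 2 years after baseline.

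The article describes the length of the basic course in two ways. Setting says: "All programs are initiated by a school-based basic course lasting 20–25 weeks". Background says that vocational programmes "consist of a short basic course (typically 10–40 weeks) followed by a main course". Background also says that about half of vocational students drop out and that most of this happens during basic training.

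Study strengths and limitations says that individual register linkage will allow the investigators to determine the intervention's "long-term effect on educational attainment".

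**The concern.** The follow-up window is 2 years, but the basic course ends well inside it and a main course follows. All three categories refer to the basic course, and none records entry to, retention in or completion of the main course. Once a student has completed the basic course, nothing that happens later in the window can move that student into the category that names dropout.

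The intervention is delivered during the basic course, so a natural long-term question is whether any gain there lasts. If some students stay to the end of the basic course and then leave, the outcome records the same result as if they had stayed in education. Conversely, a true effect on main-course retention would not be seen. What is at stake is how far the dropout result can be interpreted, and specifically whether it can carry a conclusion about educational attainment.

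**Working it through.** The article states no figure that depends on this definition, so there is none to reproduce. The check has three steps.

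**1. Assign each path to a category** (definitions from Outcome measures, one category per student).

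| Path by 2 years | Category |
|---|---|
| Completes basic course, still in or has completed further training | (a) |
| Completes basic course, then leaves education | (a) |
| Still in basic course, or changed to another upper secondary education | (b) |
| Leaves basic course, no other upper secondary education | (c) |

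The second path does not fit (b), because the student is neither still in the basic course nor in another education. It does not fit (c), because the student did not drop out of the basic course. The first two paths therefore cannot be told apart.

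**2. Time left in the window after the basic course** (2 years = 104 weeks).

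- With 20 to 25 weeks (Setting): 104 − 25 = 79 and 104 − 20 = 84 weeks remain, or 79/104 = 76% to 84/104 = 81% of the window.
- With 10 to 40 weeks (Background): 104 − 40 = 64 and 104 − 10 = 94 weeks remain, or 64/104 = 62% to 94/104 = 90%.

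On either description, most of the window falls after a completer's category is settled.

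**3. Illustration of how many students this could concern.**

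- Total dropout D = 0.50 (Background, about half).
- Share s of dropout that occurs in the basic course: Background says only that it is most, with no percentage. *Assumed* range 0.55 to 0.90.
- Later leavers as a share of all entrants = D × (1 − s).

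| s (assumed) | Dropout in basic course, D × s | Later leavers, D × (1 − s) |
|---|---|---|
| 0.55 | 27.5% | 22.5% |
| 0.70 | 35% | 15% |
| 0.90 | 45% | 5% |

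For each assumed s, the last column is an upper figure. It treats all later dropout as falling within 104 weeks, although Background gives no time horizon for its one-half, and it ignores re-entry to education.

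**The case against.** The strongest case on the other side has four parts.

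*The basic-course focus is reasonable.* The participants are basic-course students, the surveys fall in the first week and at 10 weeks, and most dropout is said to occur in basic training. This stands. A reader might infer that the primary outcome is invalid or that its between-group comparison is biased. The article supports neither: the comparison is valid for what it measures.

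*The article never calls completion of the basic course a success.* This also stands. It lists three categories and does not say how they will be grouped or modelled, which an article may leave to an analysis plan. The point needs only that (c) is the one category naming dropout and that later leavers cannot reach it.

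*The outcome does use later status.* This is right for (b) and (c), which depend on continued registration, switching or attaining another education. Because basic courses are flexible in duration, a long window is useful for them. It would be too strong to say that the outcome ignores the 2-year follow-up. Only (a) carries no later status.

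*The Discussion sentence concerns what linkage makes possible, not the three categories.* This does not hold up. Linkage could give 2-year status, but the three categories are the only register outcome the article defines, so they are all that the stated conclusion can rest on.

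**Conclusion.** The point holds in a limited form. The register outcome measures dropout from the basic course. It cannot distinguish dropout that was prevented from dropout postponed until after the basic course, and so does not by itself support a conclusion on long-term educational attainment. That rests on the definitions alone and needs no assumption.

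The size does need assumptions. With total dropout of about 50% and 55% to 90% of it in the basic course, at most about 5% to 22% of entrants would be later leavers not counted as dropout. The number is smaller if some leave after 2 years or return to education.

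Two further readings go beyond the article. A reader might infer that the intervention merely delays dropout; nothing in the article shows this, and the point is only that the outcome could not detect it. A reader might also set the 5% to 22% against a target effect of 10 points, taking 20% of one-half. No such target is stated. Sample size applies the 20% reduction to students considering dropping out, at 19%, which is 0.20 × 19 = 3.8 points, and sets no target for register dropout. For the same reason, no effect on the sample size can be computed from the article's figures.

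**What to change.** Keep the basic-course outcome as it is. From the same register linkage, pre-specify one supporting outcome at 2 years: enrolled in or having completed a main course or any other upper secondary education, versus neither. This splits category (a) into students still in or through education and students who left after the basic course. Reported beside the primary outcome, it would show whether a basic-course effect persists.

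If this is not done, limit the sentence in Study strengths and limitations to the effect on basic-course completion or dropout.

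The first option costs one derived variable and one further model, with no new data collection. Its downside is one additional supporting outcome to report and interpret. The second costs one edited sentence, but leaves the longer-term question unanswered.

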### Measures on the causal pathways

#### Intervention implementation

Process data were collected to determine the implementation degree [42]. For each class, the teachers completed a questionnaire, which addressed implementation questions measured in two ways: (i) Have essential prescribed intervention components been delivered (e.g., the students had to work in groups on an assignment relevant to their education) with response options “yes”, “no” and “don’t know”; (ii) Have the components been delivered in the intended way (e.g., the students were made to feel welcome) measured on a 10-point Likert-type scale (1 = strongly disagree to 10 = strongly agree). Strategies to facilitate the implementation were rated by the level of feedback provided to the teachers and managers (high, medium, low). Intervention implementation was also investigated as part of class observations and interviews with school staff and students, which were elements of the process evaluation carried out by researchers ([name]) in a sample of classes over the course of the study. Conclusions regarding implementation degree will be compared to these qualitative findings.

#### Immediate intervention impact

To address the immediate impact from the intervention, selected indicators regarded the introduction period (e.g., student felt welcome on the first day) and classroom management (e.g., our teachers intervene if we get distracted) were included in the student surveys.

### Personal characteristics

In addition to the outcome variables, process variables and immediate variables, the following variables were collected at baseline (see Table 1): Age, ethnic origin (determined by the place of birth of the mother, substituted by the place of birth of the father if maternal birthplace was missing and substituted by the place of birth of the student if both maternal and paternal birthplaces were missing), ethnic identity [43], parental education level [44], family social class with two items on father’s and mother’s employment status and two items on father’s and mother’s occupation, and minutes spent travelling to the school. To measure quantitative aspects of social relations, we used items from the Danish National Health Survey studies [36] to ask about how often the students have contact to friends, the students’ living situation and having children. To measure qualitative aspects of social relations, we included social support measured as the extent to which the students had someone to talk to when they had problems or needed support [36] and a HBSC item about frequency of feeling left out. To measure health behavior and health [36], we included cigarette smoking, alcohol consumption, cannabis use and use of illicit drugs other than cannabis, self-confidence and self-rated health. To measure the students’ educational background, we included academic self-efficacy [45], self-evaluated school performance, assessment of Danish reading and writing (separately) and overall prior school satisfaction

### Sample size

Sample-size calculation was performed to determine the number of classes needed in order to be able to detect a difference between the intervention and comparison group with respect to student well-being, smoking and school dropout [46]. From a nationwide student satisfaction survey in 2010 at Danish vocational schools, we selected measures on daily smoking (yes, no), consideration of dropping out (yes, no), and two indicators on student well-being: solidarity among students (yes, no), and a positive welcoming atmosphere created by the school (yes, no). Overall, 41 % were daily smokers, 19 % considered dropping out, 17 % reported a lack of student solidarity, and 21 % reported a lack of a positive welcoming atmosphere. We estimated the intra-class correlation to 0.006 for welcoming atmosphere, 0.05 for student solidarity and smoking, and 0.016 for dropout considerations. With a desired power of 80 %, a 5 % significance level, a two-sided test, and an expected 20 % reduction for each outcome in the intervention group, the minimum number of classes in intervention and comparison groups was calculated as ranging from 60 to 110. To be conservative, we chose the highest number of clusters (i.e., classes, *n* = 110). Another necessary assumption for the power calculation was that each class had an average of 20 students. Allowing for 20 % non-respondents, a total of about 5,280 students needed to be included.

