## Methods

### Study design

Shaping the Social employed a non-randomised cluster controlled design with four intervention schools and six comparison schools. Comparison schools continued with their usual practice.

Intervention schools were selected by convenience sampling; the four schools involved in the development phase of the intervention agreed to become intervention schools. We chose this strategy in order to facilitate the implementation. The four intervention schools are located in major towns dispersed in Denmark and the schools are characterized as being large schools and offering a large range of technical or agricultural basic courses, for example carpenter and zookeeper. Characteristics of the intervention schools were used to select comparison schools among schools with the best match. However, a straight matched-pair design was not possible. Vocational schools in Denmark were ranked according to the following criteria: (1) at least one basic course offered for inclusion in the intervention group, (2) large school size (student population ≥ 800), (3) urban/suburban. Sixteen vocational schools were eligible. Subsequently, eight comparison schools were selected by geographic diversity. Letters explaining the study were sent to the school management, and schools expressing an interest (*n* = 7) were then visited individually. One school withdrew due to the time commitment entailed in the data collection. After selection of comparison schools, one intervention school wanted to include agricultural basic courses, which we accepted; however, the comparison schools were not selected on this criterion.

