### Evaluation methods

Initially, we will conduct scale validation of the student well-being outcome measure, which we hypothesise to be a four-factor model. Intervention effects will be evaluated by multilevel regression methods, specifically, a multilevel regression analysis accounting for the hierarchical data structure with students nested within classes in which the intervention was implemented, and classes nested within college units. We will use mediation analyses to explore the extent to which any intervention effects are mediated by changes in the measured immediate intervention impacts. The analyses will be conducted for the total study population. The smoking analysis will be repeated whereby students are analyzed according to their baseline smoking status. Analysis of subgroups will be conducted defined by age, parental socioeconomic status and basic course. To assess the stability of the available case analyses, handling of missing data will be conducted and analysis of loss to follow-up will indicate which variables to include.

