### Participant flow

In total, we included 32 college units of 10 large and diverse technical and agricultural vocational schools; a sample of approximately 22 % of all Danish technical and agricultural vocational schools. Figure 2 shows the flow of students through the recruitment and analysis phase. The baseline survey resulted in responses from 2,329 students from four intervention schools and 3,371 students from six comparison schools, representing 73 % and 81 %, respectively, of the students assumed to be eligible. The true rate is likely to be higher because, as is typical, a number of students never started, despite enrolment on the class list, and were thus not eligible for inclusion. The majority (95 % and 97 %, respectively) who were in school on the day of data collection did respond to the questionnaire. Forty-eight students were excluded because of two or more errors identified in the data control (e.g., they reported smoking ≥ 70 cigarettes per day). The response rates for the follow-up questionnaire survey were 58 % and 52 %, respectively. The response rates of reporting the personal identification number (necessary for linkage with the education register to obtain dropout at the second follow-up) were 91 % and 88 %, respectively.

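### The sample size counts classes as independent clusters although whole schools, four against six, were assigned, so 80% power for each outcome is not supported

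*Protocol article*

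**What the plan says.** In the Sample size section the unit is the class: "Sample-size calculation was performed to determine the number of classes needed". The targets are given as "With a desired power of 80 %, a 5 % significance level, a two-sided test, and an expected 20 % reduction for each outcome". The required numbers span 60 to 110 classes across the four indicators, and the section ends with "To be conservative, we chose the highest number of clusters (i.e., classes, *n* = 110". It assumes 20 students per class and one ICC per outcome, without naming the level to which that ICC refers.

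Assignment was at a different level. Study design says "Shaping the Social employed a non-randomised cluster controlled design with four intervention schools and six comparison schools". The intervention "schools were selected by convenience sampling; the four schools involved in the development phase" of the programme, so all classes and departments of a school sit in the same group.

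The analysis uses yet another level. Setting says that "the upper analyze level will be these departments within schools (named college units", and Evaluation methods describes "students nested within classes in which the intervention was implemented, and classes nested within college units". Participant flow gives the counts: "we included 32 college units of 10 large and diverse technical and agricultural vocational schools".

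**The concern.** Classes in one school share its intervention status. Any variance between schools enters the comparison divided by 4 and 6, not by 110 and 110. The calculation has no term for this, and none for the college units that the authors themselves model because departments typically have their own premises and culture. Several components, such as common breaks and a smoke-free place to gather, also act above the level of the single class.

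If the 80% is taken at face value, a null result would look like fair evidence against a 20% reduction when the design may have had much less chance of detecting one.

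**Working it through.** **Inputs (Sample size section).** Comparison rates p0: smoking 0.41, dropout considerations 0.19, lack of solidarity 0.17, lack of welcoming atmosphere 0.21. ICCs: 0.05, 0.016, 0.05, 0.006. Intervention rate p1 = 0.8 × p0. Two-sided 5%, 110 classes per group, 20 per class, hence 2,200 students per group.

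**The plan's own figures.** 110 × 2 × 20 × 1.2 = 5,280, so 110 is per group and nothing above the class enters. The usual two-proportion formula (pooled variance under the null) gives 542, 1,540, 1,759 and 1,363 students per group. Multiplying by 1 + 19 × ICC (1.95, 1.304, 1.95, 1.114) and dividing by 20 gives about 53, 100, 172 and 76 classes. The stated range of 60 to 110 is not reproduced, and solidarity lies well above it.

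**Model with a higher level.** Let s be the assumed share of the stated ICC that lies at the higher level, rs = s × ICC, rc = ICC − rs, v1 = p1(1 − p1), v0 = p0(1 − p0), and k1, k0 the numbers of higher-level units:

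Var(difference) = v1[rs/k1 + rc/110 + (1 − ICC)/2200] + v0[rs/k0 + rc/110 + (1 − ICC)/2200]

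Schools: k1 = 4, k0 = 6; normal test, or noncentral t with 4 + 6 − 2 = 8 degrees of freedom (df). College units: k1 = 13, k0 = 19 (the split of the 32 is assumed, roughly 4:6); t with 30 df. The document gives no school or unit ICC, so s is an assumption and is varied.

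**Worked example: dropout considerations, s = 25%, schools.** Difference 0.19 − 0.152 = 0.038; v1 = 0.1289, v0 = 0.1539; rs = 0.004, rc = 0.012.
- First term: 0.1289 × (0.001000 + 0.000109 + 0.000447) = 0.000201.
- Second term: 0.1539 × (0.000667 + 0.000109 + 0.000447) = 0.000188.
- Standard error √0.000389 = 0.0197; ratio 0.038/0.0197 = 1.93.
- Power: 49% (normal), 40% (8 df).
- With s = 0 the standard error is 0.01295 and the ratio 2.93, giving 84% (normal).

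**Results.** Power at shares of 10% / 25% / 50%:

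| Indicator | Class only, normal | Schools, normal | Schools, 8 df | College units, 30 df |
|---|---|---|---|---|
| Smoking | 98% | 80 / 55 / 35% | 69 / 45 / 29% | 93 / 84 / 69% |
| Dropout considerations | 84% | 66 / 49 / 34% | 55 / 40 / 27% | 76 / 68 / 58% |
| Solidarity | 61% | 34 / 21 / 14% | 28 / 18 / 12% | 48 / 37 / 28% |
| Welcoming atmosphere | 92% | 86 / 77 / 63% | 76 / 65 / 52% | 89 / 86 / 81% |

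At a 5% school share with 8 df, smoking has 81%, welcoming atmosphere 80% and dropout considerations 63%.

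The df matter by themselves. With no school variance, 8 df alone takes dropout considerations from 84% to 73% and smoking from 98% to 94%.

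**Ceiling with unlimited classes in the same ten schools** (only the rs terms remain; 8 df; shares 10 / 25 / 50%): smoking 91 / 55 / 32%, dropout considerations 93 / 59 / 34%, solidarity 45 / 21 / 13%, welcoming atmosphere above 99 / 97 / 77%.

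**The case against.** The strongest reply is that the size of the loss is assumed. No school-level ICC is given, and the stated ICC is not even labelled as a class ICC. The 8 df also belong to a school-level test that the article does not plan: its model stops at the 32 college units. There smoking keeps 84% or more up to a 25% share, and welcoming atmosphere stays above 80% throughout. Comparison schools were chosen to resemble the intervention schools in size, urban setting and courses, and baseline differences are to enter the analysis, so residual school variance may be smaller than an unadjusted calculation implies. Finally, 80% is called a desired power, and baseline collection is over.

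Most of this stands as a limit on magnitude. Two stronger readings that a reader might infer are not supported:
- That more classes in the same schools could never restore 80%. At small school shares they could, as the ceilings show; only at larger shares is this true.
- That smoking and welcoming atmosphere certainly fall short. That depends on the school share and on the degrees of freedom.

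The reply does not rescue the calculation. A college-unit model treats units of one school as independent although they share one assignment, and the calculation lacks even that level. Nor is this a matter of condensation: the article names its clusters, calls the choice conservative and gives a total that leaves no room for another term.

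**Conclusion.** The sample-size calculation leaves out both the level at which the intervention was assigned and the upper level of the planned analysis, so its 80% power for each of the four indicators is unsupported.

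- **Solidarity** misses 80% with no assumption about schools at all (61%).
- **Dropout considerations** miss it at every tabulated share, whether placed between schools or between college units. With a normal test they drop below 80% once the school ICC exceeds about 0.0003.
- **Smoking and welcoming atmosphere** are conditional: about 80% or more if the school share is about 5% or less (8 df), and clearly less at the larger shares between schools.

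The omission can be read directly from the article. The percentages below the class-only column rest on assumed shares, an assumed 13 to 19 split of units, equal cluster sizes and no covariate adjustment.

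**What to change.** - Withdraw the unqualified claim of 80% power for a 20% reduction in each outcome.
- Restate power and detectable difference per outcome for four against six schools, and for the planned college-unit level, over a range of school and unit ICCs that includes low values.
- Take those ICCs from the 2010 nationwide survey if it identifies schools and departments; otherwise label them as assumptions.
- Name the level of the ICCs already quoted, and state the degrees of freedom used.

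The cost is a recalculation, one revised paragraph and a less favourable stated power. No new schools and no further data collection are asked for.
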